### Variables

An overview of the time points at which each variable is assessed is provided in Table 1.

#### Main predictor

##### Sleep bruxism

Sleep laboratory PSG-AV together with self-report and clinical examination is currently considered to lead to a definite diagnosis of SB.^
7
^ PSG-AV recordings enable quantification of SB-specific muscle activity, i.e., rhythmic masticatory muscle activity of masseter and/or temporal jaw muscles, as well as exclusion of non-SB-specific muscle activity, e.g., swallowing and scratching.^
34
^ However, it is difficult to use the PSG-AV for large sample studies due to feasibility and financial considerations.^
35
^

As alternatives to PSG-AV, various types of ambulatory recorders of masticatory muscle activity have been developed. Those have the obvious benefits of a natural home setting and low costs, and have been used in clinical studies, although specificity of the SB-specific muscle activity assessment remains a limitation.^
35
^ Therefore, muscle activity assessed with ambulatory recorders is considered a proxy for a SB diagnosis.

In our study, SB is assessed by measuring the EMG activity of the right temporal muscle during sleep with an ambulatory EMG recorder (Grindcare, version 3+ DL, Delta Danish Electronics, Light & Acoustics, Hørsholm, Denmark), at the home setting of the individual.^
35
^ Grindcare is a device designed for the management of SB and consists of a sensor (the portable unit which registers EMG activity and can be attached to the individual’s clothing) and the electrode (which attaches to the skin over the temporal muscle and is connected with the recording device by a wire). It can detect and record muscle EMG activity and issue a weak electrical stimulus on the skin, aimed at eliminating bruxism activity. For the purposes of this study, the issue of electrical stimuli is turned off and the device is used in its diagnostic mode. Within the Grindcare 3+ DL device, the EMG signal is amplified 808 times and bandpass filtered between 200 and 650 Hz. The signal is then converted by an analogue-to-digital converter within a range of 0–1.5 V and stored on a microSD card, from which it can be transferred and stored on an personal computer for further analysis. There are three sessions of sleep recordings (T_1_, T_3_ and T_5_), each consisting of three consecutive nights. The first session will start at the day of the baseline measurements. The second session takes place at 6 weeks from baseline, and the third session at 12 months from baseline. During their presence in the clinic, participants will be thoroughly trained on the function of the Grindcare device and placement of the electrode on the area of greatest distension of the right temporalis muscle by one examiner (MT). In addition, they will be provided with a clearly written and illustrated instruction manual to aid in the proper use of the device. At the start of each recording, participants are instructed to perform three maximum voluntary clenches in maximum intercuspation, each lasting for at least 3 s, with 10 s of rest between them. Within 2 weeks after each recording session, the device is returned to the examiner (MT), who will transfer the raw EMG data to a personal computer. The EMG signal will be assessed for the presence of an acceptable signal-to-noise ratio (i.e., >10), during a sufficient length of the recording (i.e., at least 75% of the length of the recording), and absence of artefacts, such as loss of the electrode, by custom-made software, designed for this purpose by the software engineer of the department of Oral Kinesiology of ACTA. If one or more recordings fail, they will be repeated as soon as possible, and no longer that 2 weeks after the first raw EMG data have been evaluated.

The raw EMG data will be analysed for the calculation of SB outcomes upon completion of the entire follow-up period of the study, using a stepwise analysis tool incorporated in the BruxismDetector software. This software has been developed at the Department of Oral Kinesiology of ACTA. The beginning of the sleep period will be defined as 30 min after electrode placement, and the end at moment when the EMG signal starts to exhibit an unstable pattern prior to electrode removal. During total sleep time, EMG amplitudes >20% of the highest maximum voluntary clenche will be selected for SB episode scoring, according to the Lavigne *et al.*
^
10
^ criteria. Type of SB episodes will be scored as follows: phasic (at least three suprathreshold EMG bursts lasting ⩾0.25 and <2.00 s, and separated by two interburst intervals of <2.00 s), tonic (one EMG burst lasting⩾2.00 s) or mixed (both phasic and tonic types of bursts). When the time interval between two bursts is ⩾2.00 s, a new episode is considered to start.^
10
^ Per recording, two SB outcome variables will be derived, viz., the number of bruxism episodes per hour of sleep (Epi h^−1^), and the bruxism time index (i.e., the total time spent bruxing divided by the total sleep time, times 100%).^
9,36
^

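### Both sleep-bruxism indices are scored over, and divided by, all of sleep time, although an accepted night may hold up to 25% of signal below the study's own quality limit

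*Protocol article*

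**What the plan says.** All the relevant text is in the protocol article, Materials and methods, Main predictor, Sleep bruxism.

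**Acceptance of a recording.** "The EMG signal will be assessed for the presence of an acceptable signal-to-noise ratio (i.e., >10"; this must hold "during a sufficient length of the recording (i.e., at least 75% of the length of the recording". The same sentence adds a second condition: "and absence of artefacts, such as loss of the electrode, by custom-made software". Recordings that do not pass are done again: "If one or more recordings fail, they will be repeated as soon as possible".

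**Sleep period.** The start is set by the clock: "The beginning of the sleep period will be defined as 30 min after electrode placement". The finish is read from the trace itself, namely "the end at moment when the EMG signal starts to exhibit an unstable pattern prior to electrode removal".

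**Scoring.** "During total sleep time, EMG amplitudes >20% of the highest maximum voluntary clenche will be selected for SB episode scoring". A single burst of 2 s or more is a tonic episode, with no upper limit on its length.

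**Indices.** There are two per recording: episodes per hour of sleep, and a bruxism time index, defined as "the total time spent bruxing divided by the total sleep time, times 100" per cent.

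No sentence says what happens to low-ratio stretches inside a recording that passes. The two terms of the signal-to-noise ratio are not defined.

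**The concern.** The acceptance rule and the scoring rule do not fit together. The first tolerates signal that fails the study's limit for up to 25% of a recording. The second treats every minute of the sleep period as equally scorable, in both numerator and denominator.

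Two errors can follow, in opposite directions. Where the muscle signal is too weak to register, true episodes are lost while the time still counts in the denominator. Where noise rises above the amplitude threshold, it is scored as muscle activity.

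The two indices are the exposure in all three null hypotheses (technical complications, biological complications, biofilm diversity). Participants place the electrode themselves at home, so signal quality may differ between people and nights. An error that recurs in one person would not be averaged away over nights.

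**Working it through.** **The plan's own figure.** The only computed figure in the article is the sample size: 50 + 8 × 6 = 98, which is reproduced. It does not depend on the signal rule and neither supports nor weakens this point.

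**Inputs from the article.** Ratio above 10; at least 75% of the recording; sleep starts 30 min (0.5 h) after electrode placement; amplitude threshold 20% of the highest clench; 3 sessions × 3 nights = 9 nights.

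**Assumed, because the article gives no figures.** Recording length L of 6 to 9 h; true rate 1 to 4 episodes/h; false-episode rate in poor signal 0 to 10 per hour; between-person coefficient of variation (CV) 0.4 to 1.2; unstable end of negligible length.

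**Step 1: share f of sleep time below the limit, in the worst passing recording.** The 75% rule applies to the recording, but scoring applies to the shorter sleep period.

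- All poor signal inside the sleep period, f = 0.25L / (L − 0.5): for 6 h, 1.5/5.5 = 27.3%; for 9 h, 2.25/8.5 = 26.5%.
- The excluded first 30 min is all poor signal, f = (0.25L − 0.5) / (L − 0.5): for 6 h, 1.0/5.5 = 18.2%; for 9 h, 1.75/8.5 = 20.6%.

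**Step 2: episodes only missed.** Observed/true = 1 − f. At f = 25% this is 0.75; at f = 27.3% it is 0.73. With acceptable time as the denominator it is (1 − f)/(1 − f) = 1.00, provided bruxism is spread evenly over the night.

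**Step 3: noise scored as episodes.** Observed rate = true × (1 − f) + false × f. With f = 25%:

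| True rate per h | False rate 0 | False rate 2 | False rate 10 |
|---|---|---|---|
| 1 | 0.75 | 1.25 | 3.25 |
| 2 | 1.5 | 2.0 | 4.0 |
| 4 | 3.0 | 3.5 | 5.5 |

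The direction depends on whether the false rate is below or above the true rate. For the time index, noise continuously above threshold over 25% of sleep adds at most 0.25 × 100 = 25 percentage points. One unbroken run of that kind is a single tonic burst, so episodes per hour would hardly rise.

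**Step 4: when can noise cross the threshold?** If the ratio means highest clench over noise amplitude (an assumption), noise as a share of clench is 100/ratio: 10% at a ratio of 10, 20% at 5, 33% at 3. Stretches with ratios between 5 and 10 fail the quality limit, but their noise stays below the scoring threshold.

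**Step 5: loss of information if episodes are only missed.** Let X* = X·u, where u is the acceptable share, independent of X, with mean m = 0.875 and variance v. In units of the mean of X, Var(X*) = (1 + CV²)(m² + v) − m², and the correlation of X* with X is m·CV/√Var(X*). Its square is the share of R-squared kept.

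| Acceptable share u | v | CV 0.4 | CV 0.8 | CV 1.2 |
|---|---|---|---|---|
| Uniform on 0.75 to 1 | 0.25²/12 = 0.0052 | 95.3% | 98.3% | 98.9% |
| Half at 0.75, half at 1 | 0.125² = 0.0156 | 87.1% | 95.0% | 96.7% |

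Example, second row, CV 0.4: Var = 1.16 × 0.78125 − 0.765625 = 0.140625; correlation = 0.35/0.375 = 0.933; squared, 0.871. Averaging over nine nights would reduce the loss further where quality varies from night to night.

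**The case against.** **The acceptance rule has more than one screen.** It also requires absence of artefacts, and failed recordings are repeated. Electrode loss, the most obvious fault, should be caught there. This stands, though the syntax leaves open whether the artefact check covers the whole recording. It does not close the gap: if it removed every stretch below the limit, the 75% allowance would have no function.

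**The software may already mask poor segments.** Scoring uses a stepwise tool whose steps are not described, and a condensed article may leave such steps to the operating procedures. This is the strongest counter-argument, and it means that what the software actually does is unknown. But the article does not merely stay silent: it states the scoring window, the denominator and the parts left out. If masking is done, the printed definition is wrong and still needs correcting.

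**The damage may be small.** This largely stands for missed episodes alone, as Step 5 shows. That estimate does not cover noise scored as bruxism, or quality that is related to bruxism.

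**Stronger inferences that the article does not support.** A reader might infer that up to a quarter of each night is unusable, or that the main predictor is in fact distorted. The text says only that the ratio need not exceed 10 there. It gives no distribution of signal quality, and some of the poor signal may fall in the excluded start or end. A reader might also infer that all sub-limit noise is scored as bruxism; on the clench-over-noise reading this is not so for ratios between 5 and 10.

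**Conclusion.** The concern holds as a mismatch between two stated rules: an accepted night may contain up to 25% of signal below the study's limit, and the printed definitions count that time in full. This can bias both indices in accepted nights.

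The worst-case bound for missed episodes is a reading about 25 to 27% low, assuming 6 to 9 h recordings and no detectable episode in the poor stretches. In the other direction, the time index could rise by up to about 25 points, but only with noise continuously above threshold; on the clench-over-noise assumption this needs ratios of about 5 or below. These are limits for the worst passing night, not expected values.

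The typical effect is probably modest: about 87 to 99% of R-squared is kept if quality is unrelated to bruxism and episodes are only missed. The sample size of 98 is unaffected. The change is worth making because it concerns the main predictor of every hypothesis and is inexpensive.

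**What to change.** In the Sleep bruxism section, state that:

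- stretches with a signal-to-noise ratio not above 10 are masked before scoring;
- episodes and bruxing time are counted only in acceptable signal;
- the denominators are acceptable sleep time: episodes per hour of acceptable sleep, and bruxing time / acceptable sleep time × 100%;
- the ratio is defined (which signal, which noise, over what window);
- the 75% rule applies to the sleep period and remains the condition for accepting a night.

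If the software already masks such stretches, correcting the printed definitions is enough for the first three items.

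**Cost.** One added step in the in-house software. Raw EMG is stored and scored only after follow-up ends, so the rule can be applied uniformly to all recordings, with no new data and no change to the sample size.

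**Downsides.** Up to a quarter of a night less is scored. The corrected rate assumes that bruxism is similar in masked and unmasked sleep. A few nights accepted on the recording-length rule may just fail on the sleep-period rule (72.7 to 73.5% acceptable in the worst case of Step 1), possibly after the two-week window for repeats has closed. The text should say how those nights are handled.

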#### Outcomes

##### Biological complications

Biological complications will be assessed by examining cardinal features of peri-implant health, i.e., bleeding on probing, probing depths and marginal bone height.^37
^ Also, loss of osseointegration will be registered.

Peri-implant bleeding on probing will be scored per implant according to the Modified Gingival Index^
38
^ as follows:

- Score 0; no bleeding when a periodontal probe is passed along the gingival margin adjacent the implant;- Score 1; isolated bleeding spots visible;- Score 2; blood forms a confluent red line on margin;- Score 3; heavy or profuse bleeding.

Peri-implant probing depths will be scored using a standardised periodontal probe (Click-Probe 3/5/7/10 blue, KerrHave, Bioggio, Switzerland) with pressure of 0.2–0.25 N. Clinical probing depth will be measured in millimetre as the distance from the mucosal margin to the bottom of the deepest clinical probing site on each side of the examined implant (mesial, distal, buccal and lingual). Per implant, the mean value of those sides is calculated.

Marginal bone height will be assessed radiographically. Vertical bitewing radiographs will be taken using the parallel cone technique and phosphor plates (VistaScan Image Plate, Dürr Dental, Bietigheim-Bissingen, Germany), with the assistance of individually modified plate positioning devices. Modification of the positioning devices will aim at acquiring geometric reproducibility of the radiographs during the successive examinations of the participants. More specifically, reproducing the intraoral position of the device will be achieved by using a silicone (Provil Novo, Putty regular set, Heraeus Kulzer, Hanau, Germany) mould, made just after the suprastructure is placed. A reproducible position of the X-ray tube with respect to the plate positioning device will be acquired by the use of a customised hard plastic aiming block. Radiographs are taken with a dental X-ray generator operated at 63 kV DC, 8 mA, and exposure time of 0.32 s. The obtained images will be imported in a commercial dental image archiving program (Emago, Oral Diagnostic Systems, Amsterdam, The Netherlands). Marginal bone height will be measured on each radiograph using the appropriate tool of the program as the vertical distance (mm) from a fixed landmark point on an implant (implant shoulder) to the superior border of the marginal bone at each of the mesial and distal sides of the implant. The Subtraction technique of the Emago software will be used to detect differences in marginal bone between subsequent radiographs. Measurements will be performed by two independent examiners. Per implant, the mean value of both sides is calculated.

Mobility of the implants or their suprastructures will be assessed manually by clinical investigation using the back part of the handles of two hand instruments (e.g., mouth mirror and probe). Mobility will be scored as either present or not. When mobility is present, the examiner will investigate and note the cause of mobility, i.e., technical complication(s) or loss of osseointegration.

Throughout the course of the study, if any of the aforementioned conditions require treatment, usual care will be provided.

##### Technical complications

Implant technical complications will be assessed by clinical and radiographical examination. The following complications will be registered:

Suprastructure complications (complete or incomplete fracture of veneer, fracture of framework, loosening of occlusal screw or fracture of luting cement, fracture of occlusal screw).Abutment complications (loosening or fracture of abutment screw, fracture of abutment).Implant fracture.Other complications (e.g., loss of occlusal screw seal).

In case any of these complications occur, the treating dentist will be informed and appropriate treatment will take place.

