### Study design

The study has a prospective, double-blind design and will be performed in the Academic Centre for Dentistry Amsterdam (ACTA), The Netherlands. Aimed duration of the study is 3 years: 1-year sampling period and 2 years of follow-up. Participants of the study will receive one or more dental implants, which will be loaded with a fixed dental prosthesis for replacement of one or more lost teeth. Baseline assessment (T_1_) of each participant will take place after the healing period of the implant(s), at the appointment of taking the impressions for the prosthesis. Afterwards, assessments will take place within a follow-up period of 2 years at pre-fixed time intervals (2 weeks; T_2_, 6 weeks; T_3_, 3 months; T_4_, 12 months; T_5_, and 24 months after baseline; T_6_, see Table 1). These assessment intervals match those of the regular clinical procedures at ACTA, with the exception of T_3_, which represents an additional examination. Recurrent ambulatory EMG recordings for the diagnosis of SB will be performed by the participants in their home environment at T_1_, T_3_ and T_5_. Clinical measurements will be performed by one examiner (MT) at ACTA. This examiner, as well as the participants, will be blinded for the main predictor of the study, i.e., SB diagnosis based on EMG recordings.

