#### Single/multiple analysis

Our hypotheses will be tested using multilevel regression analyses.^
32
^ As for the main aim of the study, hypotheses about associations between SB and the occurrence of technical complications or loss of osseointegration will be tested by using a Cox proportional hazards regression model.^
48
^ Possible associations between SB and bleeding on probing, pocket depths and marginal bone height will be tested by means of linear regression analysis. Likewise, for our secondary aim, possible associations between SB and microbiome diversity will be tested by means of linear regression analysis. The regression models will be expanded to examine the effects of confounders and covariates on the associations between main predictor and main outcomes. We aim to adjust our analysis for dependency of data, which arises from the fact that multiple implants can be placed in one subject, thus violating the assumption of independent observations.^49
^

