## Figures and Tables

**Table 1 tbl1:** Overview of examination time points and variables collected

*Time point (time from baseline)*	*Variables collected*
T_0_ (0)	Sleep bruxism, modified gingival index, peri-implant probing depth, marginal bone height, loss of osseointegration, modified plaque index, submucosal biofilm samples, awake bruxism, smoking status, periodontal parameters.
T_1_ (2 weeks)	Modified gingival index, peri-implant probing depth, marginal bone height, loss of osseointegration, modified plaque index, periodontal parameters.
T_3_ (6 weeks)	Sleep bruxism, modified gingival index, peri-implant probing depth, marginal bone height, loss of osseointegration, technical complications.
T_4_ (3 months)	Modified gingival index, peri-implant probing depth, marginal bone height, loss of osseointegration, technical complications, submucosal biofilm samples.
T_5_ (12 months)	Sleep bruxism, modified gingival index, peri-implant probing depth, marginal bone height, loss of osseointegration, technical complications, modified plaque index, submucosal biofilm samples, awake bruxism, smoking status, periodontal parameters.
T_6_ (24 months)	Modified gingival index, peri-implant probing depth, marginal bone height, loss of osseointegration, technical complications.

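### As described, technical complications are found only by examination at four visits, two of them covering the last 21 of 24 months, so events repaired between visits may go unrecorded

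*Protocol article*

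**What the plan says.** Under Technical complications, the article gives the method for this main outcome: "Implant technical complications will be assessed by clinical and radiographical examination". The registered events include veneer fracture (complete or incomplete), loosening of occlusal or abutment screws, fracture of luting cement and loss of the screw seal, alongside framework, abutment and implant fracture. The treating dentist is told when one occurs. No flow of information back from the dentist is described.

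Under Study design, "Clinical measurements will be performed by one examiner" at the study centre, and "assessments will take place within a follow-up period of 2 years at pre-fixed time intervals". The later visits are at "3 months; T_4_, 12 months; T_5_, and 24 months after baseline; T_6".

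Table 1 lists technical complications in four rows:
- 6 weeks: "modified gingival index, peri-implant probing depth, marginal bone height, loss of osseointegration, technical complications"
- 3 months: "loss of osseointegration, technical complications, submucosal biofilm samples"
- 12 months: "loss of osseointegration, technical complications, modified plaque index, submucosal biofilm samples, awake bruxism, smoking status, periodontal parameters"
- 24 months: the same examination items as at 6 weeks.

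Under Covariates and confounders, the dental record is named as the source for morphological and restorative features of the implants, for baseline description only.

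Under Single/multiple analysis, "the occurrence of technical complications or loss of osseointegration will be tested by using a Cox proportional hazards regression model". Under Descriptive statistics, the incidence of technical complications is to be reported.

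**The concern.** The method fits lasting damage better than transient events. The Introduction itself classes loss of retention, loss of screw-hole sealing and chipping as minor, and abutment screw loosening and veneer fracture as intermediate. Such events can be put right when the patient notices them. Once a screw is re-tightened, a crown recemented, a chip polished or a seal replaced, a later examination or radiograph may show little or nothing.

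Followed as written, the plan could count a participant with an interim repair as having had no complication. Two things are at stake for the first hypothesis: the reported incidence, and the number of events in a Cox model that will have few. Separately, an event that is still present at the 12- or 24-month visit has an onset known only to within 9 or 12 months, unless a date is obtained from elsewhere.

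**Working it through.** **Inputs.** Visits recording technical complications: 6 weeks and 3, 12 and 24 months (Table 1). Participants: 98 (Sample size). Complication rate: up to 38.7% at 5 years, for all complication types with fixed dental prostheses (Introduction), the only such rate in the article. The share of later events missed is assumed.

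**The plan's own figure.** 50 + 8 × 6 = 98, as stated. The rule involves no event count, hazard ratio or power, so there is no planned number of events to check against.

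**Coverage.** 12 − 3 = 9 months and 24 − 12 = 12 months. Together 21 of 24 months (87.5%) are covered by two examinations.

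**Expected first events, full capture** (constant hazard, one first event per participant, no dropout, time at risk from baseline):
- h = −ln(1 − 0.387)/5 = 0.0979 per year
- by 24 months: 98 × (1 − exp(−2 × 0.0979)) = 98 × 0.1778 = 17.4
- by 3 months: 98 × (1 − exp(−0.25 × 0.0979)) = 2.4
- after month 3: about 15.1, or 86% of the total.

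**Events missed**, as 20–50% (assumed) of those after month 3:

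| 5-year rate | Total by 24 months | After month 3 | Missed at 20–50% |
|---|---|---|---|
| 38.7% (article, 'up to') | 17.4 | 15.1 | 3.0–7.5 |
| 20% (assumed) | 8.4 | 7.3 | 1.5–3.6 |
| 10% (assumed) | 4.0 | 3.5 | 0.7–1.8 |

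The logical range is wider: from no loss, if every repair is traced, to about 86–87% of events, if none after month 3 is recorded.

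**Precision.** By Schoenfeld's formula (two-sided 0.05, assumed 50:50 exposure split, assumed hazard ratio 3, ceiling rate), power is 0.63 with all 17.4 events. It is 0.53 if 25% of the later events are missed (13.7 remain) and 0.41 if 50% are missed (9.9 remain).

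**Direction of bias.** Take assumed event rates of 0.055 and 0.165 per year over 21 months (1.75 years), with every event equally likely to be recorded:
- full capture: (1 − exp(−0.28875))/(1 − exp(−0.09625)) = 0.2508/0.0918 = 2.73
- half capture: (1 − exp(−0.144375))/(1 − exp(−0.048125)) = 0.1344/0.0470 = 2.86.

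The risk ratio does not move towards 1. The ratio of recorded hazards stays at 3, because both are multiplied by the same factor.

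**The case against.** The strongest reply is that the article is silent rather than exclusionary. It nowhere says that events between visits are left out. Participants are patients of the study centre's own clinic, all visits except T3 match its regular procedures, a dental record exists for each participant, and standard operating procedures are said to be extensively documented. The examiner may well ask about interim repairs. This stands to the extent that no loss can be asserted as fact. It does not dispose of the point: the article does state the method and timetable for this main outcome, and gives the dental record a different, baseline-only use.

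A reader might infer that the missed events fall more on participants with high sleep-bruxism activity and pull the association towards none. The documents do not support that. Someone with repeated events has more interim repairs but also more chances of detection, and equal thinning leaves the hazard ratio unchanged. Bias towards none would need a higher chance of an unrecorded repair per event in bruxers. The article gives no reason for that, and both examiner and participants are blinded to the EMG-based diagnosis.

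Three further objections stand in part. The rate is the top of a range, covers all complication types and refers to fixed dental prostheses, while the cohort also includes single crowns, so the counts are illustrative. That repairs leave little trace is a clinical judgement not found in the article; it applies less to a replaced crown or visibly repaired veneer, and is not argued for implant, abutment or framework fractures. How event times are defined and interval censoring handled may belong to an analysis plan that is not shown. Even so, a plan cannot supply onset dates that were never collected.

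**Conclusion.** The point holds as a weakness in how a main outcome is ascertained. As described, two examinations cover 21 of 24 months and no source is named for complications treated in between. Repairable events may go unrecorded, which would lower the reported incidence and the Cox event count. Events found at the two late visits have an onset known only to within 9 or 12 months.

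The size of the loss cannot be derived from the article. About 3–8 of roughly 17 first events is an illustration that rests on the article's upper rate, a constant hazard and an assumed 20–50% missed; lower rates give fewer. Because baseline is the impression appointment, before the prosthesis is in place, the calculation also counts slightly too much time at risk. What remains is possible under-counting, lost precision and imprecise timing. No direction of bias in the hazard ratio is claimed.

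**What to change.** At T3–T6, take technical complications from three sources:
- the examination, as now;
- the study centre's dental record since the last visit;
- one question to the participant on any repair or unscheduled visit concerning the prosthesis, including elsewhere.

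Record the type of each event under the existing categories, with its date. Use that date as the event time in the Cox analysis, or the interval between visits where the date is unknown. If interim events are already collected under the operating procedures, say so and name the source.

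The cost is protocol wording and a short record check at existing visits, with no added visit or procedure. Repairs done elsewhere would depend partly on participant recall. The examiner who does the check is already blinded to the sleep-bruxism diagnosis, and the EMG outcomes are calculated only after follow-up ends, so blinding is unaffected.
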